### Data analysis

#### Qualitative data analysis

To address our research question about IPC and ABS barriers and facilitators, qualitative data generated through individual interviews, CFS administration, follow-up interviews and implementation check-ins, and quarterly RITs will be analyzed using thematic analysis [63] based on open (i.e., inductive) as well as framework-informed (i.e., deductive) coding. To assess tailoring fidelity, RIT data representing information about locally identified implementation barriers and facilitators, as well as selected implementation strategies, together with any changes in implementation goal setting and scope, will be extracted and integrated into hospital-specific “tailoring profiles.” These will be used to assess the degree to which tailoring work occurred prospectively, was characterized by variation, and built on matching determinant-strategy pairs that are sufficiently operationalized. A traffic light system will be used to differentiate between low, medium, and high tailoring fidelity. Building on a multiple case study design, with each hospital representing a separate case, summaries of implementation determinants and theme identification will be conducted by hospital and country. Qualitative data will be coded independently by single researchers, who will be supported by a team of three researchers, who will jointly review, discuss, and refine identified codes and themes bi-weekly.

#### Quantitative data analysis

Multilevel modeling [64] with two analytic levels (Level 1: hospital staff, Level 2: hospital) will be conducted to investigate quantitative research questions forming the core of the REVERSE implementation evaluation. Multilevel models take into account the hierarchical data structure and the resulting non-independence of observations within groups and are suitable for dealing with unbalanced data, i.e., varying numbers of staff within each hospital [65]. To determine implementation outcomes, a null model will be fitted to each outcome variable to estimate the intercept, including a 95% confidence interval representing a point and interval estimate of the average outcome of interest. To determine tailoring effectiveness, outcomes will be predicted by group membership, investigating mean differences between basic vs. enhanced implementation while statistically controlling for the pretest scores and the effect of time to adjust for potential confounding of calendar time and intervention. All analyses will be conducted separately for months 3, 6, and 10 post-IPC and -ABS, and for month 20 post-IPC.

Restricted maximum likelihood estimation (REML) method with Kenward-Roger correction [66] will be used to estimate model parameters and standard errors. This method avoids small sample biases and has been shown to maintain the nominal Type-I error rates in data with Level 2 sample sizes below 25 [67]. All models will be estimated in R [68] using the *lme4* [69] and *lmerTest* [70] packages.

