### Participating hospitals and their randomization

Based on findings and modeling of the 2016/2017 ECDC point prevalence survey [51], mean estimated incidence densities of HAIs due to a composite index incorporating carbapenem-resistant Enterobacterales (CRE), carbapenem-resistant Pseudomonas aeruginosa (CRPA), and carbapenem-resistant Acinetobacter baumannii (CRAB) combined for Greece, Italy, Romania, and Spain were 2.99/1000 patient-days, 0.73, 0.62, and 0.51, respectively. Considering the lowest incidence density of 0.5/1000 patient days, an intra-cluster correlation of 0.9, four randomization steps, and 25,000 admissions per year on average, it is estimated that 24 acute care hospitals will provide sufficient power (standard power [80%] and alpha [0.05] values were used) to perform all relevant comparisons for the primary outcome as specified in Table 4. This includes the hypothesis that enhanced implementation will have an added effect on the primary outcome on top of a 35% impact of the combined IPC- and ABS-bundles, leading to an additional 15% in HAI reduction.

The 24 REVERSE hospitals were recruited based on the aforementioned 2016/2017-point prevalence survey [51], reflecting a high prevalence of MDROs in these hospitals, specifically of CRE, CRPA, or CRAB. These carbapenem-resistant organisms (CROs) represent a particularly severe threat to the health of patients due to the limited availability of treatment options. Each hospital will participate in REVERSE with approximately 350 beds that are part of intensive care, internal medicine, hematology-oncology, or surgery (including transplant) units. Pediatric and obstetrics/gynecology wards are excluded.

The trial coordinator (AS) will randomize hospitals to four cohorts of six hospitals, stratified by country (using the Stata *randtreat* package) and implementation condition (using the R *minirand* package). Each cohort will contain hospitals from every country and an equal number in both implementation arms. Hospitals will not be informed about which arm they belong to. The four cohorts will enter the trial at four different time points, as outlined in Fig. 3. Hospitals will first implement IPC and, 1 year later, begin the implementation of ABS.

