#### Facilitated tailoring (enhanced)

Additionally, implementation teams from hospitals in the enhanced implementation condition will receive *three 1-h online educational group sessions* focused on learning and discussing how to prospectively tailor local implementation work, with each meeting focusing on a particular aspect of tailoring. Implementation team members from all three hospitals in the enhanced implementation condition of a cohort will attend these sessions together to enable knowledge exchange across hospitals, each of which will be located in a different country and representing a different hospital culture. It will also be emphasized for these sites that further support from the research team can be requested at any time, be it as part of implementation-related brainstorming, problem-solving, data analysis, or similar activities. Implementation planning tasks will be assigned between meetings. Finally, the REVERSE research team will provide implementation teams from hospitals in the enhanced condition with feedback on their quarterly reporting of implementation progress for both practice bundles.

Groups of at least three research team members, involving minimum one clinical and two implementation experts, will deliver kick off and implementation calls.

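### The arm-comparison model leaves out country, a randomisation stratifier; for the staff surveys, which list no pre-start round, this may cost power or leave country imbalance unadjusted

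*Protocol article*

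**What the plan says.** Under Participating hospitals and their randomization, the trial coordinator "will randomize hospitals to four cohorts of six hospitals, stratified by country" and by implementation condition. The same paragraph adds: "Each cohort will contain hospitals from every country and an equal number in both implementation arms". Equal arms within each country are not stated. Facilitated tailoring (enhanced) says of the three enhanced hospitals in a cohort: "each of which will be located in a different country".

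Under Quantitative data analysis, the model has hospital staff at level 1 and hospital at level 2. For tailoring effectiveness, "outcomes will be predicted by group membership, investigating mean differences between basic vs. enhanced implementation", controlling for pretest scores and time. Each survey month is analysed separately. Country is not mentioned.

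Table 4 and the text on quantitative measures place the three survey scales (IUS, FIM, CSAT) at months 3, 6, 10 and 20 after IPC start and months 3, 6 and 10 after ABS start. The target is ten respondents per hospital per round, not necessarily the same people each time. Table 5 shows that translation routes differ by language and scale.

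**The concern.** A factor that restricts the randomisation and may predict the outcome normally belongs in the analysis model. If it is left out, its variance stays in the between-hospital residual. When arms are balanced over that factor, the true sampling error of the arm difference does not contain this variance but the estimated standard error does. Intervals are then too wide and the test rejects too seldom.

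The model is written for staff responses, so the surveys are where this matters. A pretest score would absorb stable country differences, but the schedule lists no round before either bundle starts. A month-3 score used as pretest would already follow the start of the arm contrast. Each test rests on 24 hospitals, so lost precision is not easily recovered.

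**Working it through.** **The plan's own figure.** The documents give no precision or power figure for the surveys and no country difference in survey scores. The one power statement (24 hospitals, 80%) concerns infection rates. It cannot be rebuilt uniquely, because patient-days, period length and the scale of the added 15% are not given. A parallel 12 v 12 calculation gives power of 0.22 to 0.998 if the 15% is in percentage points, or 0.11 to 0.87 if relative. A stepped-wedge formula gives 0.86 to 0.99 for a 15% reduction. The figure is neither confirmed nor refuted, and it does not bear on the survey question.

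**Inputs.** From the protocol: 24 hospitals, 12 per arm, ten respondents per hospital per round. Assumed: outcome SD 1, ICC 0.1 or 0.2, country share of between-hospital variance 0% to 50%, six hospitals per country.

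**Formula.** Variance of a hospital mean = ICC + (1 − ICC)/10.
- ICC 0.1: 0.10 + 0.90/10 = 0.19
- ICC 0.2: 0.20 + 0.80/10 = 0.28

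The SE ratio after removing a share s of the between-hospital part is √[(variance − s × ICC)/variance].
- ICC 0.1: s = 25%, √(0.165/0.19) = 0.93; s = 50%, √(0.14/0.19) = 0.86
- ICC 0.2: s = 25%, √(0.23/0.28) = 0.91; s = 50%, √(0.18/0.28) = 0.80
- s = 0: ratio 1

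**Simulation.** Arms split 3:3 within each country, no pretest, true difference 0.5 SD, at least 2,000 runs per row. Each pair is arm only / arm plus country.

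| ICC | Share | Model SE | Type I error | Power |
|---|---|---|---|---|
| 0.1 | 0% | 0.176 / 0.176 | 0.049 / 0.050 | 0.76 / 0.75 |
| 0.1 | 25% | 0.174 / 0.164 | 0.034 / 0.046 | 0.80 / 0.83 |
| 0.1 | 50% | 0.171 / 0.150 | 0.025 / 0.047 | 0.80 / 0.87 |
| 0.2 | 0% | 0.213 / 0.213 | 0.048 / 0.046 | 0.60 / 0.59 |
| 0.2 | 25% | 0.210 / 0.193 | 0.037 / 0.056 | 0.62 / 0.67 |
| 0.2 | 50% | 0.207 / 0.172 | 0.026 / 0.054 | 0.67 / 0.79 |

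At 50% share the simulated SE falls by 12% (0.150/0.171 = 0.88) and 17% (0.172/0.207 = 0.83), a little less than the formula's 14% and 20%. With four countries of six, the arm-only residual carries only 3 × 6/22 = 0.82 of the country variance. The formula is therefore an upper guide.

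**If arms are not balanced by country.** A cohort's three enhanced hospitals lie in different countries, so over four cohorts a country can have at most four. With six hospitals per country, a 4:2 split in one country and balance across the other three combined, a mean shift δ in that country moves the unadjusted arm difference by δ × (4/12 − 2/12) = δ/6. When allocation was not balanced by country, the arm-only model had type I error of about 0.05 to 0.06 in simulation. Its SE is then not too wide, but the realised imbalance stays in the estimate.

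**Infection rates, with the stated pretest term.** Simulated SE was 0.085 to 0.131 without country and 0.083 to 0.133 with it. Power at rate ratio 0.77 was 0.47 to 0.82 v 0.46 to 0.82. Country adds nothing there.

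**The case against.** - **The documents give no size for country differences in survey scores.** This stands. Translation routes make differences plausible but do not measure them, and at a share of 0% nothing is lost.
- **Balance of arms within country is not stated, so the SE may not be too wide.** This stands for the conservative-test argument. It does not remove the case for adjustment, because without balance the country term corrects chance imbalance.
- **The model already adjusts for pretest.** This holds where a pretest exists. None is listed for the survey scales. The Contextual Factors Survey is given before bundle start, but it is a different instrument.
- **Covariate lists may be left to an analysis plan that is not shown.** Country may be added there. But this section already fixes levels, covariates, estimator, degrees-of-freedom correction and software, and a design factor is absent from the stated list.
- **The error is in the safe direction.** With balanced arms there is no bias and no type I inflation, which limits the weight of the point.

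A reader might also infer a large loss for the primary outcome, because the planning rates "were 2.99/1000 patient-days, 0.73, 0.62, and 0.51, respectively", a range of 2.99/0.51 = 5.9-fold. The documents do not support that. The range concerns infection rates and comes from one country; the other three span 0.73/0.51 = 1.43-fold. The quoted model is for staff responses. If it is applied to infection rates, the pretest term in the same sentence absorbs stable country differences, as shown above.

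**Conclusion.** The point holds for the staff survey scales, as an efficiency and balance improvement. The stated arm model omits a stratifier of the randomisation, and no listed survey round can stand in for it as a pretest. The formula puts the SE reduction from adding country between 0% and 20%. At a 50% share, simulated power for a 0.5 SD difference rises from 0.80 to 0.87 (ICC 0.1) or from 0.67 to 0.79 (ICC 0.2).

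These figures rest on assumed ICCs, country shares and six hospitals per country. The power figures also assume arms balanced within country. The conclusion is that power may be lost, not that it is. Confidence is moderate. For infection rates with a pretest or baseline rate in the model, there is no material loss.

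**What to change.** Add country as a fixed effect (3 df) to the arm-comparison models, above all for the IUS, FIM and CSAT scales, and state this before the comparison is run.

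The cost is one model term and three between-hospital degrees of freedom. From 22 to 19, the critical t rises from 2.074 to 2.093 (0.9%). If time is coded by cohort, the step is about 19 to 16, and it rises from 2.093 to 2.120 (1.3%). If country explains nothing, simulated power falls by about 0.01 (0.76 to 0.75 at ICC 0.1).

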### Study outcomes, measures, and their administration

The REVERSE implementation evaluation focuses on different targets and outcomes. These are listed in Table 4, according to the research question they are linked to, together with the measure to be used for their assessment and the frequency with which they will be administered.

**Table 4 Tab4:** REVERSE implementation evaluation outcomes, measures, and their administration

#	Research question	Outcome/target	Outcome measure	Administration
1	Is facilitated, tailored implementation of IPC and ABS superior to basic implementation of IPC and ABS, i.e., does it lead to significantly better clinical and implementation outcomes when compared with basic implementation?	Primary: Healthcare-acquired infections (HAIs)	- Incidence density per quarter (N/1000 patient-days) of HAIs due to CRE, CRPA, and CRAB, combined in a composite index - Incidence density per quarter (N/1000 patient-days) of HAIs due to ESBL, MRSA, and VRE combined in a composite index	- HAIs: prospective data collection for all microbiologically confirmed HAIs by the organisms of interest in all participating REVERSE wards
		IPC/ABS usability	- Intervention Usability Scale (IUS)	- Months 3, 6, 10, and 20 post IPC start, and months 3, 6, and 10 post ABS start
		IPC/ABS feasibility	- Feasibility of Interventions Measure (FIM)	- Months 3, 6, 10, and 20 post IPC start, and months 3, 6, and 10 post ABS start
		IPC/ABS sustainability	- Clinical Sustainability Assessment Tool (CSAT)	- Months 3, 6, 10, and 20 post IPC start, and months 3, 6, and 10 post ABS start
2	What are the anticipated and actual contextual barriers and facilitators of implementing IPC and ABS in acute care hospitals with a high prevalence of antimicrobial resistance located in different regions in Italy, Spain, Greece, and Romania?	Implementation context/determinants	- REVERSE Contextual Factors Survey (CFS) - CFS follow up interview with local IPC/ABS team	- 8 months prior to IPC and ABS start - 4 months into IPC and ABS implementation
			- Online check-ins with local IPC/ABS team	- 6 months into IPC and ABS implementation
			- Site visits including individual stakeholder interviews and hospital rounds	- Enhanced sites only - One site visit prior to IPC start - One site visit prior to ABS start

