For each language, the three measures will be integrated into one tool that will be administered with all REVERSE hospitals (*N* = 24) three times during IPC and three times during ABS implementation, namely in months 3, 6, and 10. Since the duration of IPC implementation is set for 2 years, one additional measurement will be conducted in month 20 to assess whether stakeholder perceptions change at a later stage of the implementation and a time when the work with ABS has been added. At each point of administration, the REVERSE study nurses will be asked to distribute a link to the survey among implementation team members and other relevant hospital staff involved in the local implementation of both practice bundles in their respective hospitals. The intended minimum sample size per round of survey administration is *n* = 240, i.e., ten respondents per hospital and round of administration. Since hospitals’ implementation work will change over time, it is not the intention to include the same respondents in every round of survey administration.

*Intervention fidelity* describes “the degree to which interventions are put into practice as intended” [58], which in the REVERSE trial refers to both practice bundles. To measure practice bundle fidelity—within the field of IPC and ABS, often referred to as *adherence* [38, 59]—a set of clinical process indicators has been defined for each practice bundle, thereby following common approaches to monitoring the quality of care in this field [60]. Table 6 provides an overview of these clinical process indicators for REVERSE IPC.

**Table 6 Tab6:** Clinical process indicators for REVERSE IPC

**SOP***	**Process indicator**	**Reporting**
**HH**	WHO Hand hygiene Self-Assessment	Annually
	Alcohol hand rub consumption	Quarterly
	HH compliance	Quarterly (Minimal requirement: 3 HH observations sessions per unit quarterly)
**CP**	% of patients requiring CP who are actually under CP	Quarterly (Minimal requirement: 1 observation per ward per quarter)
	% compliance (infrastructure, placement, equipment)	Quarterly (Minimal requirement: 10 observations [i.e., 10 patients] per quarter)
**IC**	% of patients requiring IC who are actually under IC (according to hospital’s own policy of who requires IC). Specified by MDROs	Quarterly (Minimal requirement: 6 point-prevalence-audits per quarter)

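### The basic-versus-enhanced model for the staff surveys adjusts for pretest scores that the schedule never collects, so it cannot be fitted as written

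*Protocol article*

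**What the plan says.** Under Quantitative data analysis, the protocol article describes multilevel models with hospital staff at level 1 and hospital at level 2. There are two kinds. A null model estimates the average of each outcome. A second model compares basic with enhanced implementation while "statistically controlling for the pretest scores and the effect of time to adjust for potential confounding of calendar time and intervention". The timing is explicit: "All analyses will be conducted separately for months 3, 6, and 10 post-IPC and -ABS, and for month 20 post-IPC".

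Table 4 gives the administration of IUS, FIM and CSAT, under research questions 1 and 3 alike, as "Months 3, 6, 10, and 20 post IPC start, and months 3, 6, and 10 post ABS start". The text of the same section agrees: the combined tool is given "three times during IPC and three times during ABS implementation, namely in months 3, 6, and 10", and "one additional measurement will be conducted in month 20 to assess whether stakeholder perceptions change at a later stage of the implementation". On respondents it says that "it is not the intention to include the same respondents in every round of survey administration", and on numbers: "The intended minimum sample size per round of survey administration is *n* = 240, i.e., ten respondents per hospital and round of administration".

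**The concern.** The analysis section relies on a covariate that the data-collection section does not provide. This is a conflict between two positive statements. It is not a detail left for an analysis plan, because a plan cannot supply scores that were never scheduled.

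The model concerned is the stated test of tailoring effectiveness on the implementation outcomes, and so part of research question 1. An analyst told to adjust for a pretest must either drop the term or find a substitute. The earliest score for either bundle is month 3. That score is taken after randomisation and probably after the facilitation calls given only to the enhanced arm. Adjusting for it could remove part of the effect that the trial sets out to measure. A substitute picked once data are in hand would also leave the choice open to influence from the results.

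**Working it through.** **1. Survey size.** 24 hospitals × 10 respondents = 240 per round, as the protocol states.

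**2. Rounds before bundle start.** IPC rounds fall at months 3, 6, 10 and 20 after IPC start: 0 of 4 precede it. ABS rounds fall at months 3, 6 and 10 after ABS start: 0 of 3 precede it. ABS starts one year after IPC, so the ABS rounds fall at 12 + 3 = 15, 12 + 6 = 18 and 12 + 10 = 22 months after IPC start. The month-3 IPC model has no earlier score of any kind. The ABS models have earlier scores only from IPC rounds, which rate another bundle and follow IPC facilitation.

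**3. Other possible pretests.**
- HAI incidence is a hospital rate per quarter. It is not a staff-level score and does not measure usability, feasibility or sustainability.
- The Contextual Factors Survey is given 8 months before each bundle, but it is a 46-item context questionnaire with Likert, yes/no and free-text items. The article defines no summary score for it and does not call it a pretest.

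**4. Is month 3 after facilitation?** Table 2 puts training in the month before start and the enhanced-arm calls 3, 6 and 9 weeks after team formation. The date of team formation is not stated. Teams form after training and attend the kick-off call 2 to 3 weeks after it, so I assume formation 0 to 3 weeks after training.
- Earliest third call: −4.35 + 0 + 9 = 4.65 weeks after start.
- Latest third call: 0 + 3 + 9 = 12 weeks after start.
- Month 3 is about week 13.

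On this assumption all three calls precede the month-3 round.

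**5. What adjusting for month 3 would do.** Assume different respondents in each round, 10 per hospital, a total SD of 1, and correlation r between a hospital's true levels in the two rounds. The slope of the later hospital mean on the month-3 mean is

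b = r × ICC / (ICC + (1 − ICC)/10) = r × 10 × ICC / (1 + 9 × ICC),

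and the adjusted effect is d_late − b × d_month3. If the two effects are equal, b is the share removed. Example: ICC 0.10 and r = 0.8 give 0.08 / 0.19 = 0.42. The article gives neither ICC nor r, so both are assumed.

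| ICC | r = 0.5 | r = 0.8 | r = 1.0 |
|---|---|---|---|
| 0.05 | 17% | 28% | 34% |
| 0.10 | 26% | 42% | 53% |
| 0.20 | 36% | 57% | 71% |
| 0.30 | 41% | 65% | 81% |

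A simulation (24 hospitals, 12 per arm, 5,000 runs, true later effect 0.50 SD, ICC 0.10, r = 0.8) agrees with the formula:

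| Month-3 effect (SD) | Formula | Simulated adjusted effect (SD) |
|---|---|---|
| 0.50 | 0.50 − 0.42 × 0.50 = 0.29 | 0.29 |
| 0.25 | 0.50 − 0.42 × 0.25 = 0.40 | 0.40 |
| 0 | 0.50 | 0.50 |

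**The case against.** The strongest reply is that only one covariate is undefined. The null models use no pretest and fit as written. Without the pretest term the arm comparison still fits, and randomisation keeps it valid, so the loss is precision. Table 4 labels HAIs as primary, not these scales. All of this stands. A reader might infer that no survey analysis can be run, and the protocol does not support that.

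A reader might also infer that the protocol plans to use month 3 as the baseline and so biases its later comparisons toward zero. It does not say so. It treats month 3 as an outcome to be analysed in its own right, which counts against that reading. The bias is also not certain in direction: it is nil without a month-3 effect, and away from zero if that effect has the opposite sign to the later one.

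Two further inferences go too far. Changing respondents rule out a pretest for each individual, but not a hospital-mean pretest; it is the schedule that rules out the latter. The text also says only that the same people are not intended in every round, so some overlap is possible, and the formula above assumes none.

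It might finally be said that the separate analysis plan, or the figure of study procedures (not reproduced in the text at hand), settles the matter. A plan could drop or redefine the term, but it cannot create a pre-start round. A baseline round in the figure would contradict both Table 4 and the text, and would itself need reconciling.

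**Conclusion.** The point holds in a limited form. For IUS, FIM and CSAT the arm-comparison model names a covariate that is scheduled in none of the seven rounds, so it cannot be fitted as written. This follows from the document alone and needs no assumption.

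The harm from a substitute is conditional. It requires that a post-start round be used as the pretest and that facilitation has already shifted scores by then. With equal effects at both times the loss is about 17% to 81% over the assumed ranges, and 42% at ICC 0.10 and correlation 0.8. These figures are illustrative. They assume no overlap of respondents and the same correlation whichever later month is analysed. The timing of the calls relative to month 3 is probable but not stated.

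The HAI comparison is not affected by this point.

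**What to change.** In Quantitative data analysis, and in the analysis plan if it repeats the wording:

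1. Delete the pretest term from the arm-comparison model for IUS, FIM and CSAT.
2. State that no score collected after bundle start may serve as a baseline covariate. This includes IPC rounds in the ABS models.
3. Adjust for country and cohort, both fixed before start. Cohort can carry the calendar-time adjustment: each model covers one month after start, so calendar time differs only by cohort, and each cohort has equal numbers of hospitals in the two arms.

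The cost is the precision that a true pretest would have given. An intercept, arm, three country terms and three cohort terms leave 24 − 8 = 16 degrees of freedom between hospitals. No new data are needed. A pre-start IPC round can no longer be added, at least for the first cohort, which began IPC in April 2023. The wording should be settled before any comparison by arm is run; first results are expected in 2026.
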